## 1. Background and Study rationale

Ischemic heart disease (IHD) is the single most common cause of death and its frequency is increasing globally. It is estimated that IHD is the cause of 1.8 million deaths or 20% of all deaths in Europe. Despite advancement in the fields of rapid diagnosis and in treatment strategies, the morbidity and mortality in patient with ST-segment myocardial infarction remains substantial, with an estimated mortality rate of 4-12% according to registries of the ESC countries. According to the 2017 European Society of Cardiology (ESC) guidelines for the management of acute myocardial infarction in patients presenting with ST-segment elevation (STEMI), there is a level 1 recommendation with a level of evidence A for primary percutaneous coronary intervention (PPCI) strategy in patients with STEMI, and this strategy is preferred over fibrinolytic therapy. In addition, the ESC guidelines recommend a first medical contact to reperfusion time within 60 minutes in STEMI patients for primary PCI-capable centers. This recommendation is supported by a recently published study that showed shortening door to balloon (D2B) time was significantly associated with survival benefit. Based on the recommendation for maximal D2B time in STEMI patients to be 60 minutes, many countries and institutions worldwide have been established programs, among them the national program for quality indicators by the Israeli ministry of health, to shorten D2B times. According to data published by the Israeli ministry of health regarding the year of 2018, 88% of STEMI patients had a D2B time of <90 minutes. The common practice during PPCI is to complete diagnostic angiography of the whole coronary tree before performing culprit-vessel revascularization. This practice is not evidence-based and current guidelines do not prioritize full diagnostic angiography over culprit-vessel revascularization first. As was found in previous studies, this practice might result in delaying revascularization by 4-8 minutes in D2B time. This delay might potentially lead to worse outcome in STEMI patients, although not proven in the above cited studies.

The aim of this study is to determine the magnitude of the delay and to evaluate the clinical impact of the delay in coronary revascularization in patients with STEMI treated with PPCI.

## 2. Objectives

- To determine the magnitude of delay in coronary revascularization in patients with STEMI treated with PPCI after full diagnostic angiography, in comparison with patients who underwent initially coronary culprit revascularization (PPCI) following diagnostic angiography of the non-culprit coronary arteries.

|                                                                                                                                                                                 |    |
|---------------------------------------------------------------------------------------------------------------------------------------------------------------------------------|----|
| • To assess the impact of diagnostic angiography of suspected culprit artery first versus full diagnostic angiography prior to coronary revascularization on D2B time.          | 49 |
| • To assess the impact of diagnostic angiography of suspected culprit artery first versus full diagnostic angiography prior to coronary revascularization on clinical outcomes. | 51 |
|                                                                                                                                                                                 | 52 |
| 3. Endpoints                                                                                                                                                             | 53 |
| a. Primary endpoint:                                                                                                                                                     | 54 |
| ○ Reduction in Door-to-Balloon (D2B) time                                                                                                                                       | 55 |
| Protocol amendment:                                                                                                                                                      | 56 |
| The investigators ask the IRB for a study protocol amendment due to reconsideration of study protocol and primary outcome:                                               | 57 |
| ○ Revised primary outcome: Needle-to-balloon time within 10 minutes.                                                                                                     | 58 |
| ○ Revised primary outcome: Needle-to-balloon time within 10 minutes.                                                                                                     | 59 |
| b. Secondary endpoints:                                                                                                                                                  | 60 |
| ○ Need for inotropes and/or vasopressors during PCI                                                                                                                             | 61 |
| ○ Need for mechanical circulatory support (IABP, Impella or ECMO) during PCI                                                                                                    | 62 |
| ○ Need for mechanical ventilation or non-invasive ventilation (NIV) during PCI                                                                                                  | 63 |
| 4. Study Cohort                                                                                                                                                          | 64 |
| • Estimated number of 300 patients (~150 each group).                                                                                                                           | 65 |
| a. Inclusion criteria:                                                                                                                                                   | 66 |
| ○ ≥18 years old                                                                                                                                                                 | 67 |
| ○ STEMI on arrival ECG                                                                                                                                                          | 68 |
| ○ PPCI on arrival to SZMC                                                                                                                                                       | 69 |
| b. Exclusion criteria:                                                                                                                                                   | 70 |
| ○ Cardiac arrest, CPR or ECMO on arrival to catheterization laboratory                                                                                                          | 71 |
| ○ Prior coronary artery bypass grafting (CABG) surgery                                                                                                                          | 72 |
| 6. Methods and statistical analysis                                                                                                                                      | 73 |

This is a prospective, randomized, controlled, unblinded and single-center study that will include all patients with STEMI that will be admitted to SZMC. All patients will be randomized to culprit-only diagnostic angiography group (intervention arm) versus full diagnostic angiography group (control arm) prior to revascularization during PPCI on index hospitalizations. A full diagnostic angiography will be performed only after intervention to culprit artery in the intervention arm. Data will be collected from AZMA and Clicks and be held by the PI only. Baseline patients' characteristics including age, gender, cardiovascular risk factors, previous coronary interventions, current medical treatment, and comorbidities will be collected. Procedural parameters including door-to balloon time, fluoroscopy time, amount of contrast media, number of catheters and rate of conversion to femoral access will be collected and compared between the two groups. Clinical parameters including need for inotropes or vasopressors, need for mechanical circulatory support, need for mechanical ventilation or NIV, rate of ventricular tachyarrhythmias, LVEF on first in-hospital echocardiography and in-hospital mortality rate will be compared between the two groups.

Statistical analysis will be performed using SPSS Statistics for Windows (SPSS Inc., Chicago, IL). Descriptive statistics will first be used to describe the study population data. The primary and secondary endpoints will first be studied using Chi-square or Fisher's exact tests for comparisons between the outcomes for categorical variables and the t-test or Mann-Whitney U test for continuous variables. Test selection will be based on data distribution and normalcy.

Based on previously published data, the primary outcome of a needle-to-balloon time of ten minutes or less was used for sample size calculation. The calculated sample size was a minimum of 50 patients per group to detect a 50% relative increase in the proportion of patients who achieved the primary outcome (power=0.9,  $\alpha$ =0.05,  $\beta$ =0.1).

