**Inclusion Criteria**

216

- ≥18 years old

183

184

185

186

187

188

189

190

191

192

193

194

195

196

197

198

199

200

201

202

203

204

205

206

207

208

209

210

211

212

213

214

215

217

|                                                                                                               |                   |                                                                        |            |
|---------------------------------------------------------------------------------------------------------------|-------------------|------------------------------------------------------------------------|------------|
| • ST-Elevation MI on arrival/MADA ECG                                                                         | 218               | • Cardiac arrest, CPR or ECMO on arrival to catheterization laboratory | 221        |
| • Primary PCI on arrival to SZMC                                                                              | 219               | • Prior CABG                                                           | 223        |
| Exclusion Criteria                                                                                     | 220               |                                                                        |            |
| i. Basic Information                                                                                   |                   |                                                                        | 224        |
| 1. Patient's Code ___                                                                                         | 225               | 5. Date of Birth __/__/____ (dd/mm/yyyy)                               | 230        |
| 2. Patient's Group ___ (1-Culprit First 2-Culprit Last)                                                       | 226
227        | 6. Ethnicity ___ (1-Jewish 2-Arab 3-Other)                             | 231        |
| 3. ID Number _____                                                                                            | 228               | 7. Date of Hospital Admission __/__/____ (dd/mm/yyyy)                  | 232
233 |
| 4. SZMC Accession Number _____                                                                                | 229               |                                                                        |            |

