| 5. Initiation of Hemodialysis __ (0-No 1-Yes)                  | 374        |                                                                      |            |

|                                                      |     |                                                    |
|------------------------------------------------------|-----|----------------------------------------------------|
| 10. PEA/Asystole __ (0-No 1-Yes)                     | 381 | 14. Mechanical Circulatory Support __ (0-No 1- 387 |
| 11. Non-Invasive Ventilation __ (0-No 1-Yes)         | 382 | IABP 2-Impella 3-ECMO) 388                         |
| 12. Mechanical Ventilation __ (0-No 1-Yes)           | 383 | 15. In-Hospital Death __ (0-No 1-Yes) 389          |
| 13. Mechanical Complication __ (0-No 1-Acute 384     |     | 16. 30-Day All-Cause Death __ (0-No 1-Yes) 390     |
| MR 2-Ventricular Septal Rupture 3-LV Free 385        |     |                                                    |
| Wall Rupture) 386                                    |     |                                                    |
| ix. Pre-Discharge Echocardiography            |     | 391                                                |
| 1. Left-Ventricular Ejection Fraction __ (%) 392     |     | 3. Apical Thrombus __ (0-No 1-Yes) 396             |
| 2. Grade of Mitral Regurgitation __ (0-No MR 1- 393  |     |                                                    |
| Mild MR 2-Mild-Moderate MR 3-Moderate 394            |     |                                                    |
| MR 4-Moderate-Severe MR 5-Severe MR) 395             |     |                                                    |
| x. Hospitalization Information                |     | 397                                                |
| 1. Monitoring Level at Admission to ICCU __ (1- 398  |     |                                                    |
| Level I 2-Level IIa 3-Level IIb 4-Level III) 399     |     |                                                    |
| 2. Length of Hospitalization in ICCU __ (days) 400   |     |                                                    |
| 3. Length of Hospitalization in Cardiology Dept. 401 |     |                                                    |
| __ (days) 402                                        |     |                                                    |
| 4. Total Length of Hospitalization __ (days) 403     |     |                                                    |

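### LVEF is compared between arms of an unblinded trial and nothing masks the echo reading; masking the routine reader would close this bias route for a small change in workflow.

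*Combined protocol and SAP*

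**What the plan says.** Section 6 describes the design: "This is a prospective, randomized, controlled, unblinded and single-center study". No assessor is excepted. After the procedural measures it names the clinical comparisons, ending: "LVEF on first in-hospital echocardiography and in-hospital mortality rate will be compared between the two groups". On data handling it says: "Data will be collected from AZMA and Clicks and be held by the PI only".

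The case report form holds one LVEF value, "1. Left-Ventricular Ejection Fraction", in the section headed "ix. Pre-Discharge Echocardiography". It has no field for the reader, a second reading or masking. The arm is entered in section i of the same form: "Patient's Group ___ (1-Culprit First 2-Culprit Last".

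No part of the documents says who reads the echocardiogram, what that person can see, or whether a core laboratory is used. Section 3 does not list LVEF: the revised primary outcome is needle-to-balloon time within 10 minutes, and the three secondary endpoints are support measures needed during PCI. Section 2 does make the effect on clinical outcomes an objective.

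**The concern.** The operators cannot be masked to the order of angiography and PCI, but an echo reader can be. The plan treats the study as unblinded throughout and does not use that option.

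LVEF is a percentage that a person reports from a scan. It is also the only continuous measure among the clinical parameters that section 6 names; the others are events that occur or do not. The background section gives a direction of expectation, since it suggests that the delay from full angiography first might worsen outcome. A reader who knows the sequence and shares that expectation could lean towards the culprit-first arm without intending to. Randomisation does not protect against a reading that differs by arm, and the planned t-test or Mann-Whitney test cannot tell such a shift from a true difference.

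What is at stake is the credibility of any LVEF difference the trial reports, not its primary result.

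**Working it through.** **The plan's own figure.** There is none for LVEF. The only calculated size, 50 per group in section 6, is for the primary outcome. The control rate behind it is not given, so it cannot be confirmed, and nothing below depends on it being right.

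**Inputs from the documents**
- About 150 per arm (section 4) and a minimum of 50 per group (section 6); both are used.
- Alpha 0.05 (section 6). Sidedness is not stated; two-sided is assumed, so the critical value is 1.96.
- t-test or Mann-Whitney test for continuous variables (section 6). A normal approximation to the two-sample comparison of means is used.

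**Assumed inputs**
- LVEF SD of 9, 10 or 11 points.
- No true difference between arms.
- A net between-arm reading shift b of 1 or 2 points, averaged over all scans.

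**Formulas**
- SE = SD × √(2/n)
- Chance of a false significant benefit in the favoured direction = 1 − Φ(1.96 − b/SE)

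With b = 0 this is 1 − Φ(1.96) = 2.5%.

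**Results**

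| n per arm | SD | SE | b = 1 | b = 2 |
|---|---|---|---|---|
| 150 | 9 | 1.04 | 15.9% | 48.6% |
| 150 | 10 | 1.15 | 13.7% | 41.0% |
| 150 | 11 | 1.27 | 12.0% | 35.0% |
| 50 | 9 | 1.80 | 8.0% | 19.8% |
| 50 | 10 | 2.00 | 7.2% | 16.9% |
| 50 | 11 | 2.20 | 6.6% | 14.7% |

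One cell in full: n = 150, SD 10, b = 1 gives b/SE = 1/1.155 = 0.866, and 1 − Φ(1.96 − 0.866) = 1 − Φ(1.094) = 13.7%.

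**Wider SD range.** With SD 8-12 at 150 per arm, b = 1 gives 11-19% and b = 2 gives 30-58%. At 50 per arm the ranges are 6-9% and 13-24%.

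**Dilution.** The shift b is an average over all scans. If a quarter of scans were read by someone aware of the arm, and those readings produced a 2-point difference between arms, then b = 0.25 × 2 = 0.5. At 150 per arm and SD 9-11 this gives 5.9-7.0%. To reach b = 1 through that quarter alone would take a difference of 1/0.25 = 4 points in those scans.

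**Which scan.** Section 6 compares "LVEF on first in-hospital echocardiography". The form records "Left-Ventricular Ejection Fraction" under a pre-discharge heading. These are the same scan only if a patient has one echocardiogram in hospital. With more than one, the documents do not settle which value is analysed, and an unmasked choice would be a second route for the same bias.

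**The case against.** The strongest objection is that the mechanism is not documented. No passage says that the echo reader knows the arm. Section 6 has the data held by the principal investigator only, so the group code on the form is not shown to reach a reader. A reader of the protocol might infer that operators or other staff aware of the arm will read the scans, or that LVEF will be biased. The documents do not support that inference; they only leave the possibility open. This stands, and it limits the point to a missing safeguard.

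Second, LVEF appears once, in a list of clinical parameters, with no power or error-rate plan. One might infer that the bias threatens the trial's main conclusion. It does not: the primary outcome is a time interval, and the listed secondary endpoints do not come from the echocardiogram. This also stands.

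Third, the SD and the shift are both assumed, and the figures are largest when every scan is affected at 150 per arm. This stands too, so the smaller group size and the diluted case are shown. Even at 150 per arm, a 1-point shift usually would not reach significance.

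Fourth, it would be too strong to say that a reading bias could never be detected. The form collects first, last, maximum and minimum values of high-sensitivity troponin and CPK, which could support or contradict an LVEF difference, and nothing rules out a later masked re-reading. Neither is planned for that purpose, however, and masking at the time of reading is simpler.

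Finally, masking is neither free nor certain. Removing allocation from the echo request does not mask a reader who opens the catheterisation report. The fix therefore also sets the order of reading, and some unmasking may remain.

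**Conclusion.** The concern holds as a modest design improvement. The trial is declared unblinded without exception, a reader-dependent measure is compared between arms in support of a stated objective, and no step keeps the reader from knowing the arm.

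On the assumptions above, a net shift of 1-2 points would multiply the 2.5% chance of a false significant benefit roughly five- to twentyfold at 150 per arm (12.0/2.5 = 4.8; 48.6/2.5 = 19.4), and roughly three- to eightfold at 50 per group (6.6/2.5 = 2.6; 19.8/2.5 = 7.9). These figures show sensitivity to a shift. They do not estimate a bias known to exist, and partial exposure would reduce them. If masking removes the shift fully, the chance returns to 2.5% with no change in sample size.

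The difference between the methods and the case report form over which echocardiogram is used is documented and needs no assumption.

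**What to change.** In section 6, write: *Unblinded to operators; LVEF is read and recorded masked to allocation.* Support it with three working rules:

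- Keep allocation and angiography sequence off the echo request.
- Have the routine reader finalise LVEF before opening the catheterisation report or the group code.
- Where the existing roster allows, do not let the PCI operator read the scan of a patient he or she treated.

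In the same edit, reconcile the first in-hospital echocardiogram in section 6 with the pre-discharge heading in section ix of the case report form, so that the scan analysed is fixed in advance.

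The cost is a small constraint on echo reporting, and masking may be imperfect because the reader can still reach the clinical record. No extra reader, scan or patient is needed. The design, sample size and primary outcome are unchanged.

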| 6. Creatinine __.__(mg/dL)                                                                                                                               | 279                      | 13. International Normalized Ratio (INR) __.__(sec)                                | 286        |
| 7. Lactic Acid Dehydrogenase (LDH) ____(IU/L)                                                                                                            | 280                      | 14. Fibrinogen ____(mg/dL)                                                         | 287        |
| vi. Procedural Data                                                                                                                               |                          |                                                                                    | 288        |
| 1. MI Type __ (1-Anterior 2-Anterior-Lateral 3-
Lateral 4-Inferior 5-Inferior-Posterior 6-
Posterior 7-Diffused ST-Depression 88-
Undetermined) | 289
290
291
292 | 14. End-Case Time __:__(hh:mm)                                                     | 308        |
| 2. Day of the Week __ (1-7)                                                                                                                              | 293                      | 15. Access Site __ (1-Rt Radial 2-Lt Radial 3-Rt
Femoral 4-Lt Femoral 88-Other) | 309
310 |
| 3. Arrival to Cath Lab __ (1-Directly by MADA 2-
From ER 3-Other)                                                                                     | 294
295               | 16. Access Site Conversion __ (0-No 1-Yes)                                         | 311        |
| 4. Hour at Arrival to Cath Lab __:__(hh:mm)                                                                                                              | 296                      | 17. Culprit Artery __ (1-LM 2-LAD 3-Ramus 4-LCx
5-RCA 88-Undetermined)          | 312
313 |
| 5. First Medical Contact Time (FMCT) __
(hh:mm)                                                                                                       | 297
298               | 18. Significant LM Disease __ (0-No 1-Yes)                                         | 314        |

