|                                                                                                                                                          |                          | 27. PCI to RCA __ (0-No 1-Yes)                                                     | 323        |
|                                                                                                                                                          |                          | 28. Total Number of Stents Deployed __ (0-9)                                       | 324        |
|                                                                                                                                                          |                          | 29. Total Number of Wires Used __ (0-9)                                            | 325        |

|                                                                |            |                                                                      |            |
|----------------------------------------------------------------|------------|----------------------------------------------------------------------|------------|
| 30. Total Number of Diagnostic/Guiding Catheters Used __ (0-9) | 326
327 | 37. End-Procedural Systolic Blood Pressure __ __ (mmHg)              | 335
336 |
| 31. IC Imaging __ (0-No 1-IVUS 2-OCT)                          | 328        | 38. End-Procedural Diastolic Blood Pressure __ __ (mmHg)             | 337
338 |
| 32. FFR/IFR Use __ (0-No 1-Yes)                                | 329        | 39. End-procedural Saturation __ (%)                                 | 339        |
| 33. IIB/IIIA inhibitors administration __ (0-No 1-Yes)         | 330
331 | 40. Door-to-Needle Time __ (Min)                                     | 340        |
| 34. Total Fluoroscopic Time __ __ (Min)                        | 332        | 41. Needle-to-Balloon __ (Min)                                       | 341        |
| 35. Total Contrast Delivered __ __ (mL)                        | 333        | 42. Door-to-Balloon __ (Min)                                         | 342        |
| 36. End-Procedural Heart Rate __ __ (bpm)                      | 334        | 43. FMCT-to-Balloon Time __ (Min)                                    | 343        |
| vii. Intra-Procedural                                   |            | Complications                                                 | 344 |

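### Door-to-balloon minutes are compared without adjusting for door-to-laboratory time, which the procedure order cannot change; the comparison is unbiased but imprecise, mainly at 50 per group or for effects near 4 minutes

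*Combined protocol and SAP*

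**What the plan says.** Section 2 (Objectives) includes "To assess the impact of diagnostic angiography of suspected culprit artery first versus full diagnostic angiography prior to coronary revascularization on D2B time". Section 1 gives the expected size: "this practice might result in delaying revascularization by 4-8 minutes in D2B time". The amendment in section 3 replaced D2B reduction as the primary endpoint ("Revised primary outcome: Needle-to-balloon time within 10 minutes") but left the D2B objective in place. D2B is not among the listed secondary endpoints.

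Section 6 compares "Procedural parameters including door-to balloon time, fluoroscopy time, amount of contrast media, number of catheters" and other items between the two groups. For continuous data it names "the t-test or Mann-Whitney U test for continuous variables", chosen by distribution. It describes no covariate, no confidence interval and no power for D2B. Needle-to-balloon time appears in section 6 only as the 10-minute yes/no outcome, so D2B is the only interval to reperfusion that it names for comparison in minutes.

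The procedural section (vi) of the case report form records arrival route (item 3), "Hour at Arrival to Cath Lab" (item 4), needle time (item 12), "Door-to-Needle Time" (item 40), needle-to-balloon (item 41) and door-to-balloon (item 42).

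**The concern.** D2B is a sum of three intervals: door to laboratory, laboratory to needle, and needle to balloon. The arms differ only in the order of angiography and intervention during the procedure. The first interval reflects the route of arrival and how quickly the laboratory is reached. It can add variance to D2B but no effect of procedure order.

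That this interval supplies much of the variance is an inference. The plan works with a D2B scale of 60 to 90 minutes and a needle-to-balloon cut-off of 10 minutes, so most of the interval seems to lie before the needle. The documents give no observed split.

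At stake is how well the D2B objective is answered. A real delay of the expected size could give a non-significant difference with a wide interval, even beside a clear result on the primary outcome. The plan does not say how such a result would be read.

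**Working it through.** **The plan's own figure.** There is none for D2B. The stated minimum of 50 per group is for the binary primary outcome (50% relative increase, power 0.9, alpha 0.05). No control proportion is given, so it cannot be reproduced outright. With the usual two-sided two-proportion formula, control rates of 57% and 58% give 51 and 48 per group. It says nothing about D2B precision.

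**Inputs.** Difference of 4 to 8 minutes (section 1). Group sizes of 50 (section 6, minimum) and about 150 (section 4, planned). Alpha 0.05 (section 6); two-sided is assumed, as the plan does not say.

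**D2B SD (assumed).** The only distributional clue is the national figure, "88% of STEMI patients had a D2B time of <90 minutes". With z(0.88) = 1.175 and a normal distribution, SD = (90 − mean)/1.175:
- mean 55: 35/1.175 = 29.8
- mean 60: 30/1.175 = 25.5
- mean 65: 25/1.175 = 21.3

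A lognormal with medians 55, 60 and 65 gives 26.3, 22.6 and 19.1. I use 20-30 minutes. Centres from 45 to 70 minutes would widen this to about 15-38.

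**Power of the unadjusted t-test.** SE = SD × √(2/n); power ≈ Φ(difference/SE − 1.96). Example: SD 20, n = 50 gives SE = 20 × 0.2 = 4.0. For 4 minutes, Φ(1.00 − 1.96) = 0.169; for 8 minutes, Φ(2.00 − 1.96) = 0.516.

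| n per group | SD | SE | 4 min | 8 min | 95% CI half-width |
|---|---|---|---|---|---|
| 50 | 20 | 4.00 | 16.9% | 51.6% | 7.8 |
| 50 | 25 | 5.00 | 12.3% | 35.9% | 9.8 |
| 50 | 30 | 6.00 | 9.8% | 26.5% | 11.8 |
| 150 | 20 | 2.31 | 41.0% | 93.4% | 4.5 |
| 150 | 25 | 2.89 | 28.3% | 79.1% | 5.7 |
| 150 | 30 | 3.46 | 21.0% | 63.7% | 6.8 |

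The exact t calculation differs by less than one percentage point. For 6 minutes at 150 per group, power is 74%, 55% and 41% at SD 20, 25 and 30. Outside the main range, SD 15 gives 27% (4 min) and 76% (8 min) at 50 per group, and 64% and over 99% at 150. SD 40 gives 7% and 17%, and 14% and 41%.

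**Gain from adjustment.** If the three intervals are independent, adjusting for door-to-laboratory minutes leaves a residual SD of √(SD₂² + SD₃²), where 2 and 3 are the in-laboratory intervals. Two assumed splits with similar totals:
- Split A, SDs 22, 5, 7: total √(484 + 25 + 49) = 23.6; residual √74 = 8.6; pre-laboratory share of variance 484/558 = 87%.
- Split B, SDs 18, 8, 12: total √(324 + 64 + 144) = 23.1; residual √208 = 14.4; pre-laboratory share 324/532 = 61%.

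| n per group, effect | A raw | A adjusted | B raw | B adjusted |
|---|---|---|---|---|
| 50, 4 min | 13% | 64% | 14% | 28% |
| 150, 4 min | 31% | 98% | 32% | 67% |
| 150, 8 min | 84% | >99% | 85% | >99% |

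Simulations with skewed components agree. For 4 minutes, Mann-Whitney against adjusted power was 15-17% against 30-65% at 50 per group, and 42-44% against 68-97% at 150. The adjusted test's error rate under no effect stayed near 5%.

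**Needle-to-balloon minutes.** With an assumed SD of 6-10 minutes, power for 4 minutes is 92% to 52% at 50 per group and at least 93% at 150.

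**The case against.** The strongest reply is that the amendment has already dealt with the noise. The primary outcome now starts at the needle, and D2B is neither primary nor a listed secondary endpoint. That stands, and it limits the point to a supporting outcome. It does not remove it, because the D2B objective remains.

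Section 6 can also be read more generously. Its sentence on tests refers to the primary and secondary endpoints, so applying it to D2B is an inference. It says these tests come first, which does not exclude later adjustment, and the list of procedural parameters is open, so needle-to-balloon minutes are not ruled out. All true, but on that reading D2B has no named method at all, and the adjusted analysis is still unwritten.

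The size of the gain is not established by the documents. It follows from the assumed variance split, and the 88% figure is national, not from this center. This stands: split B cuts the gain sharply, though it does not abolish it.

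The covariate is safe only if allocation cannot affect when the patient reaches the laboratory. The trial is unblinded and the timing of randomization is not stated. This also stands and becomes a condition of the fix.

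A reader might infer that the test has little power across the whole 4-8 minute range. It does not: at the planned 150 per group, power for 8 minutes is 63-93% at SD 20-30.

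**Conclusion.** The point holds as one of efficiency. Section 6 leaves the D2B comparison unadjusted, although the form holds the fields needed to remove variance that procedure order cannot influence. Precision is poor mainly at the minimum of 50 per group, or for effects near 4 minutes at either size. At 150 per group and 8 minutes it is moderate to good.

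The conclusion rests on an assumed D2B SD of 20-30 minutes, two-sided testing, and the inference that much of the variance arises before the laboratory. None of these is stated in the documents.

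Two further readings should be resisted. The raw comparison is not biased: randomization makes it a fair estimate of the mean D2B difference, only a noisy one. Nor do the documents show that a non-significant result would be reported as no effect on D2B; they are silent on its interpretation. The change is worth making because it is cheap, not because the main result is at risk.

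**What to change.** In section 6:

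1. Analyze D2B minutes by linear regression on randomized arm, adjusted for door-to-laboratory-arrival minutes and arrival route (item 3), with robust standard errors. Report the adjusted difference in minutes with its 95% CI.
2. Derive door-to-laboratory minutes as item 40 − (item 12 − item 4), and state how the door is defined for patients brought directly to the laboratory.
3. State, as a condition for using this covariate, that allocation cannot influence laboratory arrival time or is revealed only after it.
4. Keep the raw D2B summary by arm as description.
5. Compare needle-to-balloon minutes (item 41) between arms with a 95% CI. This needs no derived covariate and also serves the first objective, the magnitude of the delay.

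The cost is a few sentences and one derived variable, with no new data or patients. The downside is that the D2B estimate becomes model-based, and its gain depends on the in-laboratory variance: at 50 per group and 4 minutes, adjusted power is only about 30-65% under the assumed splits.
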